| 
Only answer the actual suicide attempt
                                                                                                                                                                                                                                                                                                                                                                                                                                                                                                                                                                                                                                                                                                                                                                                                                                                                       | 
The most deadly suicide attempt
                                                               |
| 
Actual fatality, physical damage:
 
0 No physical damage or very light body damage (such as epidermal abrasions)
 
1 Mild physical injury (such as speechlessness, burns, mild bleeding, sprains).
 
2 Moderate physical injury; need medical attention (such as conscious but sleepy, some reactions, second degree burns, large blood vessel bleeding).
 
3 moderate to severe physical injury; hospitalization is required and may be intensive care (eg, third-degree burns that are in a state of drowsiness, good reflexes, 20% of the body area, massive hemorrhage but recoverable, severe fractures).
 
4 Severe physical injury requires hospitalization and intensive care (such as being in a state of drowsiness and losing reflex function, a third degree burn of more than 20% of the body area, a large amount of blood loss, and unstable vital signs and serious
 | 
Input code#
_____
                                                                         |

|                                                                                                                                                                                                                                                                                                                                                                                                                                                                                                                                                                                                                                                                               |                                 |
|-------------------------------------------------------------------------------------------------------------------------------------------------------------------------------------------------------------------------------------------------------------------------------------------------------------------------------------------------------------------------------------------------------------------------------------------------------------------------------------------------------------------------------------------------------------------------------------------------------------------------------------------------------------------------------|---------------------------------|
| 
damage to vital parts).
 
5 death
                                                                                                                                                                                                                                                                                                                                                                                                                                                                                                                                                                                                                                 |                                 |
| 
Potentially fatal: answer only if the actual fatality = 0
 
The actual suicide attempt may be fatal if it does not cause physical damage (the following example does not cause actual physical damage, but may have a very serious fatality: the trigger is pulled after the muzzle is placed in the mouth, but because the gun is not misfiring Causes physical damage; lies on rails that are about to come by train, but is pulled out of the rails before being run over by the train).
 
0 behavior may not cause harm
 
1 Behavior may cause harm but will not cause death
 
2 Despite medical care, behavior can still lead to death
 | 
Input code#
 
_____
 |

## Annex 7: Arizona Sexual Experience Scale (ASEX)

### Arizona Sexual Experience Scale (ASEX) - Male

| For each entry, please indicate your overall level over the past week, including today.                                                                     | Score |
|-------------------------------------------------------------------------------------------------------------------------------------------------------------|-------|
| 1. How strong is your sexual desire?
1 very strong 2 very strong 3 some strong 4 some weak 5 very weak 6 no sexual desire                                | _     |
| 2. Is your libido easily evoked (ignited)?
1 very easy 2 is easy 3 is easy 4 is difficult 1 very difficult 6 never evoked                                | _     |
| 3. Can you easily get and keep an erection?
1 very easy 2 very easy 3 some easy 4 some difficult 5 very difficult 6 never get                            | _     |
| 4. Can you easily reach orgasm?
1 very easy 2 very easy 3 some easy 4 some difficult 5 very difficult 6 never reached orgasm                             | _     |
| 5. Are you satisfied with your orgasm?
1 very satisfied 2 very satisfied 3 some satisfied 4 some dissatisfied 5 very dissatisfied 6 can not reach orgasm | _     |
| Total score  _                                                                                                                                       |       |

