#### **The secondary efficacy endpoint**

- Changes from baseline in the 17 items Hamilton Depression Scales (HAM-D17) total scores at the end of treatment.
- Clinical Global Impression – global improvement (CGI-I) scores at the end of treatment.
- Changes from baseline in the Clinical Global Impression –severity illness (CGI-S) scores at the end of treatment.
- Changes from baseline in the the Hamilton Anxiety Scale (HAMA) total scores and factor scores at the end of treatment.
- Changes from baseline in the HAM-D17 factor scores at the end of treatment.
- Response rate in MADRS at the end of treatment (Response means that the reduction in MADRS score is 50% or more relative to the baseline value).
- Response rate in HAM-D17 at the end of treatment (Response means the reduction in the HAM-D17 scores is 50% or more relative to the baseline values).
- Remission rate in MADRS at the end of treatment (Remission refers to MADRS  $\leq 12$ ).
- Remission rate in HAM-D17 at the end of treatment (Remission refers to HAM-D17  $\leq 7$ ).
- Changes from baseline in the SHEEHAN Disability Scale (SDS) total scores at the end of treatment.

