### **8.2.6 Arizona Sexual Experience Scale (ASEX)**

The sexual function of the subjects was evaluated at baseline, follow up visits and early termination of the trial, and their sexual function changes were evaluated. This questionnaire is completed by the clinician or the person who is the subject of the test.

If the patient meet any one of the following, the patient may be considered to have sexual dysfunction: Asex total score of  $\geq 19$ , any asex scores  $\geq 5$  points, any 3 asex score  $\geq 4$  points. If the patient does not meet any of the above criteria, the sexual function may be considered normal.

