**Annex 2: 17 Hamilton Depression Scale (HAM-D17)**

| Note: Most projects use a 5-level scale of 0 to 4 points. The standards at each level are: (0) no; (1) mild; (2) moderate; (3) severe; (4) extremely severe. A few projects use a 3-point scale of 0 to 2 points. The grading criteria are: (0) none; (1) light to moderate; (2) severe |                                                     |                                                                                                                                                                                                                                                                                                                                                           |       |
|-----------------------------------------------------------------------------------------------------------------------------------------------------------------------------------------------------------------------------------------------------------------------------------------|-----------------------------------------------------|-----------------------------------------------------------------------------------------------------------------------------------------------------------------------------------------------------------------------------------------------------------------------------------------------------------------------------------------------------------|-------|
| project                                                                                                                                                                                                                                                                                 |                                                     |                                                                                                                                                                                                                                                                                                                                                           | score |

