| 13              | Systemic symptoms                                                                                                                                                                                                                       | 0 = asymptomatic;
1 = heavy feelings on the limbs, back or head; back pain, headache, muscle pain; general weakness and fatigue;
2 = 2 points for any obvious symptoms                                                                   | _ |
| 14              | Sexual symptoms
(loss of libido, menstrual disorders)                                                                                                                                                                                | 0 = asymptomatic;
1 = mild;
2=severe                                                                                                                                                                                                     | _ |
| 15              | Suspected disease                                                                                                                                                                                                                       | 0 = asymptomatic; 1 = excessive attention to (physical health); 2 = repeated consideration of health issues;
3 = Frequent complaints, requests for help, etc.; 4 = Suspected delusions                                                      | _ |
| 16              | Weight loss                                                                                                                                                                                                                             | 0 = no weight loss;
1 = there may be weight loss associated with the current disease;
2 = definitely weight loss (according to the patient);
3=not evaluated                                                                          | _ |
| 17              | Self-awareness                                                                                                                                                                                                                          | 0 = know that you are sick, showing depression;
1=I know I am sick, but I blame it for poor food, environmental problems, work, viral infection or
Need to rest, etc.;
2= completely denied the disease                               | _ |

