**II. Overall Progress (CGI-I)**

At your discretion, this improvement is entirely due to the treatment of the drug. How does the patient's condition change compared to when the patient was enrolled in the interview?

0 = not rated 4 = no change

1=Advance is very obvious 5=Slightly worse

2=Advance is obvious 6=Significantly worsened

3=Slight progress 7=Deterioration is very obvious

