**Arizona Sexual Experience Scale (ASEX) - Women**

| For each entry, please indicate your overall level over the past week, including today.                                                                     | score |
|-------------------------------------------------------------------------------------------------------------------------------------------------------------|-------|
| 1. How strong is your sexual desire?
1 very strong 2 very strong 3 some strong 4 some weak 5 very weak 6 no sexual desire                                | _     |
| 2. Is your libido easily evoked (ignited)?
1 very easy 2 very easy 3 some easy 4 some difficult 5 very difficult 6 never evoked                          | _     |
| 3. Is your vagina easy to get wet during sex?
1 very easy 2 very easy 3 some easy 4 some difficult 5 very difficult 6 never become                       | _     |
| 4. Can you easily reach orgasm?
1 very easy 2 very easy 3 some easy 4 some difficult 5 very difficult 6 never reached orgasm                             | _     |
| 5. Are you satisfied with your orgasm?
1 very satisfied 2 very satisfied 3 some satisfied 4 some dissatisfied 5 very dissatisfied 6 can not reach orgasm | _     |
| Total score  _                                                                                                                                       |       |

**Annex 8: Diagnostic Criteria for Depressive Disorders in the Diagnostic and Statistical Manual of Mental Disorders, 5th Edition (DSM-5)**

**A.** During the same 2 weeks period, 5 or more of the following symptoms appear, showing different changes compared to the previous function, at least 1 of which is 1. Mental depression or 2. Loss of interest or pleasure.

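### Male ASEX item 2 prints code 1 for the fifth level, where every comparable item prints 5; scored as printed, it can class men with sexual dysfunction as normal

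*Protocol*

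**What the plan says.** Annex 7 of the Protocol prints separate ASEX forms for men and women, each with five items summed to a total. Male item 2 asks how easily arousal is evoked and offers "1 very easy 2 is easy 3 is easy 4 is difficult 1 very difficult 6 never evoked". The next item on the same form offers "1 very easy 2 very easy 3 some easy 4 some difficult 5 very difficult 6 never get", and male items 1, 4 and 5 also run from 1 to 6 without a gap. The women's form puts the same arousal question with "1 very easy 2 very easy 3 some easy 4 some difficult 5 very difficult 6 never evoked".

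Section 8.2.6 turns these scores into a classification. On any one of three conditions, "the patient may be considered to have sexual dysfunction": a total of 19 or more, any item of 5 or more, or any three items of 4 or more. A subject who meets none of them may be considered normal. The same section says that the form is completed by the clinician or the subject, and that change in sexual function is evaluated. The flow chart in Section 7 schedules ASEX at baseline, at Visits 3 to 7 and at early termination. Section 8.2 lists ASEX among the safety evaluations.

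**The concern.** A higher ASEX item score means worse function. On the male form the second-worst arousal level therefore carries the best possible score, and the code that should separate levels 4 and 6 is missing. The contradiction is internal to Annex 7 and needs no outside source to see.

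Two results are at stake for men: the ASEX total and its change from baseline, and the dysfunction classification. The classification is exposed because one item of 5 is enough by itself to meet the rule, and the misprint removes exactly that score. A recorded 1 on this item also becomes ambiguous. It may mean *very easy* or *very difficult*, and the number alone cannot tell them apart. Where the subject fills in the form, nothing on it would prompt a correction.

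**Working it through.** No sample size, power or alpha is involved. The inputs are the printed codes in Annex 7 and the three-part rule in Section 8.2.6.

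**1. Codes side by side**

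| Item | Codes for levels 1 to 6 |
|---|---|
| Male item 2, as printed | 1, 2, 3, 4, **1**, 6 |
| Male item 3 | 1, 2, 3, 4, 5, 6 |
| Women's item 2 | 1, 2, 3, 4, 5, 6 |

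**2. Effect on the total.** Printed code minus consistent code = 1 − 5 = −4 for each *very difficult* answer.

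**3. Effect on change.** Changes are written as later score minus earlier score.
- True worsening from level 4 to level 5: 5 − 4 = +1. As printed: 1 − 4 = −3, a recorded 3-point improvement.
- With level 5 at baseline and a true improvement to level 3: 3 − 5 = −2. As printed: 3 − 1 = +2, a recorded worsening.

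The error in change can therefore run either way within a patient.

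**4. Effect on the classification.** With item 2 fixed at level 5, the other four items can take 6⁴ = 1,296 patterns.
- Coded 5: all 1,296 meet the rule, because one item of 5 or more is enough.
- Coded 1: the subject is still caught if another item is 5 or more. This leaves 4⁴ = 256 patterns with all four others at 4 or less, so 1,296 − 256 = 1,040 are still caught.
- Of the 256, those with three or four items equal to 4 still meet the three-item condition: 4 × 3 + 1 = 13.
- The rest have at most two items equal to 4: none, 3⁴ = 81; one, 4 × 3³ = 108; two, 6 × 3² = 54. Sum: 81 + 108 + 54 = 243.
- The largest total among these 243 is 1 + 4 + 4 + 3 + 3 = 15, below 19, so the total does not catch them either.

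Result: 243 / 1,296 = 18.75% of patterns change from dysfunction to normal. Full enumeration of the answer patterns gives the same 243.

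**5. Examples (items 1 to 5)**
- 3, 5, 3, 3, 3: total 17, dysfunction through item 2. As printed 3, 1, 3, 3, 3: total 13, normal.
- 3, 5, 3, 4, 4: total 19, dysfunction. As printed 3, 1, 3, 4, 4: total 15, normal.

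**The case against.** The strongest reply is that this is a slip of translation or transcription. A sequence of 1, 2, 3, 4, 1, 6 shows its own gap, the wording of this row differs from the rows around it, and the annexes contain other awkward translations. The form used at the sites and the eCRF are not shown, so nothing establishes that any man was scored 1. That stands, and it is why the effect is stated conditionally and why the first action is to check the working form. It does not remove the point, because this annex is the scoring key that the Protocol supplies for a safety scale it names.

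It is also fair to say that Section 8.2.6 does not miss every such man. A man with another item of 5 or more, or with three other items of 4 or more, is still classed as having dysfunction. The count above allows for this.

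A reader might infer that the error favours the drug, since the Background presents better sexual function as an expected advantage. The documents do not support that. The same form serves all three blinded arms, the direction between arms would depend on who gives this answer and when, and Section 11.2.2.6 treats safety P-values as nominal.

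A reader might also place two other printed codes in the same class: "3=not evaluated" for HAM-D17 item 16, where the Annex 2 note says "A few projects use a 3-point scale of 0 to 2 points", and "0 = not rated 4 = no change" for CGI-I in Annex 3, with a similar 0 for CGI-S. From these one might infer wrong HAM-D17 totals, lost remissions, or a distortion as large as the phase II drug-placebo difference. That does not follow. These are labels for an unrated item and not severity levels. No section directs that they be summed or ranked, and Section 11.2.2.7 carries forward the last observation for missing HAM-D17 item scores and CGI scores, which fits reading them as missing. A shift in one patient's score is also not comparable with a difference between group means.

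**Conclusion.** The point holds for male ASEX item 2. The printed code contradicts the rest of the male form and the women's form. Scored as printed, it lowers the total by 4 for each *very difficult* answer, can reverse the sign of a change, and reclassifies 243 of 1,296 answer patterns from dysfunction to normal.

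This rests on two assumptions: that the site form or database carries the code as printed, and that the rule in Section 8.2.6 is applied to the recorded codes. The 18.75% counts every pattern equally and is not an estimate of the share of patients. The documents do not say how often men choose this level, so the number affected cannot be computed. The direction between arms is unknown.

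The reach is limited to one answer of one item, in men only, on a safety measure. MADRS, the sample size and the multiplicity procedure are untouched. For HAM-D17 item 16 and the CGI, the most that remains is a request for one clarifying line.

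**What to change.** - In Annex 7, print code 5 for *very difficult* in male item 2, and programme the eCRF to match.
- Compare the Chinese-language site form and the eCRF code list with the corrected annex. If both already use 5, only the Protocol text changes.
- If data were collected under the printed code, verify every male item 2 score of 1 against the source document before recoding. A blanket recode would be wrong, because 1 is also the valid code for *very easy*. If the source holds only the number, the value cannot be resolved and should be flagged as such.
- Add one clarifying line that HAM-D17 item 16 code 3 and CGI code 0 are missing-value codes, kept out of totals and analyses.

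The cost is a form and database correction, with source checks limited to male item 2 scores of 1 if the misprint was in use. No added patients, visits or procedures are needed.

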**Arizona Sexual Experience Scale (ASEX) - Women**

| For each entry, please indicate your overall level over the past week, including today.                                                                     | score |
|-------------------------------------------------------------------------------------------------------------------------------------------------------------|-------|
| 1. How strong is your sexual desire?
1 very strong 2 very strong 3 some strong 4 some weak 5 very weak 6 no sexual desire                                | _     |
| 2. Is your libido easily evoked (ignited)?
1 very easy 2 very easy 3 some easy 4 some difficult 5 very difficult 6 never evoked                          | _     |
| 3. Is your vagina easy to get wet during sex?
1 very easy 2 very easy 3 some easy 4 some difficult 5 very difficult 6 never become                       | _     |
| 4. Can you easily reach orgasm?
1 very easy 2 very easy 3 some easy 4 some difficult 5 very difficult 6 never reached orgasm                             | _     |
| 5. Are you satisfied with your orgasm?
1 very satisfied 2 very satisfied 3 some satisfied 4 some dissatisfied 5 very dissatisfied 6 can not reach orgasm | _     |
| Total score  _                                                                                                                                       |       |

**Annex 8: Diagnostic Criteria for Depressive Disorders in the Diagnostic and Statistical Manual of Mental Disorders, 5th Edition (DSM-5)**

**A.** During the same 2 weeks period, 5 or more of the following symptoms appear, showing different changes compared to the previous function, at least 1 of which is 1. Mental depression or 2. Loss of interest or pleasure.

